### Risk and Protective Factors

#### Overview

The scientific literature has identified well-known risk and protective factors for disabling CP. The most widely studied have been individual factors [5,33] that are “the result of historical and ongoing interactions between genetic, epigenetic, and environmental conditions, which are embedded in and shaped by multilevel social factors” [34].

However, the role of interpersonal factors—such as experiencing IPV against women versus not experiencing it—in shaping these “individual” factors is often overlooked, despite evidence recognizing interpersonal relationships as both a risk and a protective factor for pain-related dysfunction [33,35]. In the following subsections, we provide a brief overview of some of the most relevant risk and protective factors for CP and health outcomes identified in the scientific literature.

#### Gender Norms and Identity

Biological differences partially explain sex-related variations in pain perception; however, psychosocial factors such as gender norms also play a significant role. Gender norms influence differences between men and women in pain sensitivity, pain tolerance, pain expression, and coping mechanisms [36-39]. These norms shape gender identity, which refers to an individual’s social and psychological self-conception as a man or a woman [40].

A recent clinical study pointed out that gender identity, rather than genetic sex, may play a more significant role in shaping pain perception [41]. Clinical studies have found that feminine traits correlate with pain sensitivity and can predict the development of CP in men [42,43]. In addition, traits associated with femininity, such as servility or subordination, have been linked to greater disability in individuals with CP [44]. More recently, a study based on machine learning modeling identified a strong association between agreeableness and fibromyalgia [6].

#### Education and Socioeconomic Background

Research highlights socioeconomic factors—such as income, occupation, wealth, and education—as primary contributors to a wide range of health outcomes [45], including perceived pain and CP management [5,46]. In fact, socioeconomic status is inversely related to both the prevalence and severity of CP, as well as higher levels of disability [47,48].

Regarding education, having spent less time in education can influence pain in various ways, including through exposure to environmental stressors, work history, and health literacy [46]. Education level has also been linked to the overall burden on health care systems [49].

#### Ethnicity or Racialized and Minoritized Groups

Through social learning, children acquire the specific cultural meanings attached to pain, which is influenced by ethnicity [50,51]. Ethnicity impacts various aspects of pain experiences, such as pain expression, remedies, when to ask for help, and perceptions of health care systems and illness behaviors [52]; for example, children learn when it is appropriate to share pain experiences with family members and caregivers [53,54].

Studies in the United States and Europe have shown differences across ethnic and cultural groups (eg, American, British, Latinx, and South Asian) in self-reported pain intensity and coping styles [55-60]. In addition, there is increasing evidence that racism negatively affects pain perception and pain management [61-63].

#### Pain Worrying (Pain Catastrophizing)

Pain catastrophizing, now referred to as pain worrying [64], is considered one of the strongest predictors and correlates to negative pain experiences [65-69]. The higher the levels of pain worrying, the greater the intensity, severity, and emotional distress related to pain [65,70,71]. Pain worrying is also associated with a greater need for medical advice and increased health care use [72], as well as higher levels of disability [73]. It is a key factor in explaining variability in pain experiences [67] and is commonly used as a criterion to assess changes in cognition, making it an important component in interventions aimed at reducing pain and improving functioning [74]. The fear-avoidance model, one of the most accepted theories on CP, suggests that pain worrying mediates the relationship between pain and disability [75].

#### Pain-Related Self-Efficacy

Self-efficacy refers to an individual’s belief in their ability to organize and execute the necessary actions to achieve specific goals in a given situation [76]. For individuals with CP, self-efficacy is related to their belief in their ability to perform activities despite pain—referred to as pain-related self-efficacy [77]. Regardless of pain severity, improvements in pain-related self-efficacy are associated with reductions in disability [78]. Moreover, a previous meta-analysis found that pain-related self-efficacy negatively correlated with impairment, affective distress, and pain severity [79].

#### Traumatic Events

The scientific literature has strongly linked posttraumatic stress disorder (PTSD), particularly as a result of childhood trauma, to CP [23,80]. The comorbidity between PTSD and CP health issues ranges from 10% to 50% [81]. According to some studies, when CP coexists with PTSD, the pain tends to be more severe and causes greater distress, higher levels of interference, and more disability compared to cases of CP without a history of trauma [82]. PTSD is also a highly prevalent consequence of IPV against women, affecting 31% to 84.4% of women experiencing IPV [83], with similar rates found in more recent studies [84].

#### Receipt of Informal Social Support

Social support refers to the resources provided through both informal and formal relationships [85]. There is growing research on how social factors, particularly social support, influence pain experiences [86-88]. Informal social support is especially valued by patients with CP [89,90]. Within a person’s social context, spouses or partners can play a critical role in CP management as either risk or protective factors. They can promote autonomy by encouraging positive behaviors [91] or foster dependence by reinforcing disabling pain behaviors through overprotectiveness [91-93] or negative responses such as hostility and criticism [93,94]. However, negative responses are more likely to worsen pain intensity, disability, and pain behaviors when they occur in the context of low marital satisfaction [95,96].

#### Activity Patterns

Studies have identified 3 general activity patterns that affect the quality of life and CP adjustment: pacing, avoidance, and persistence [97]. These general activity patterns can be divided into more specific ones depending on the person’s goals [98,99]. However, to simplify, pacing generally involves breaking down daily activities into smaller, more manageable tasks and distributing them throughout the day. Pacing is used in clinical contexts to reduce avoidance and excessive persistence. There is strong empirical evidence that avoidance and excessive persistence contribute to worsened CP outcomes, including poorer psychological and physical functioning, increased pain [97,100], and difficulties in performing daily activities, leading to more global disability [101,102]. Avoidance is a strategy aimed at minimizing pain escalation by reducing engagement in physical activities. In cases of highly disabling CP, avoiding physical activity is common [103]. Conversely, the persistence pattern involves continuing to perform tasks despite pain, aiming to increase productivity by “ignoring” the pain [97].

#### Exercising

Exercising is a key component of the multidisciplinary treatments in CP, offering significant benefits beyond musculoskeletal health. It has been shown to reduce pain intensity and fatigue as well as improve physical function, psychological well-being, and overall quality of life [104,105]. Its benefits for CP go beyond just musculoskeletal health [106,107]. In fact, several studies have shown that exercise ameliorates pain even if the person’s strength, flexibility, or endurance does not improve [107,108]. It could be that physical exercise has analgesic effects [109].

#### CP Outcomes

How individuals manage CP can have deep and long-lasting effects on their quality of life. Effective management can minimize pain, reduce physician visits, empower patients to participate in treatment decisions, and provide a sense of control over their lives [110-114]. By contrast, poor CP management can negatively impact socialization, reduce participation in social events, and decrease independence, leading to isolation [115,116]. It can also increase vulnerability to suicide and suicidal ideation [110] as well as contribute to the misuse of both licit and illicit drugs—such as alcohol, marijuana, or heroin—for pain relief [117-119], which, in turn, further strains health systems. Pain is one of the primary reasons for medical consultations worldwide, accounting for 22% of visits [120,121]. People with CP visit their general practitioner twice as often as those without CP [122], and they are more likely to use emergency services and unscheduled care [123,124]. In Spain, CP is the second most common reason for primary care consultations, with >50% of visits related to this condition [125].

## Methods

This research project is expected to last 3 years and will be conducted in 2 phases: the first phase will involve a qualitative study (general aim 1, study 1), and the second phase will involve a quantitative cross-sectional study (general aim 2, study 2). Before commencing the studies, the web-based closed questionnaires to be completed by participants will be piloted with a sample of 10 women to address any issues related to content, usability, or technical functionality of the web-based platform used to design the questionnaires.

### Ethical Considerations

Approval has been obtained from the ethics committee of Miguel Hernández University (DCC.ANR.240227) and the Public Health Ethics Committee for Research of the Foundation for the Promotion of Health and Biomedical Research of the Valencian Community (CEI-SP 20240531/05/P).

Ethical requirements will be consistent across both studies. All participants will receive a letter with a description of the study and of the individual interview content and questionnaires that they will have to fill in depending on the study in which they participate. There will not be any incentive for participation.

For the qualitative phase (phase 1), participants will sign an informed consent form, which clearly states that participation is voluntary and that they can withdraw at any time. Before the interviews, they will have to complete a web-based questionnaire to check whether they meet the inclusion criteria. Participants will submit their informed consent to a designated professional at the relevant health center, unit, or association, who will assign a code to each participant and will also be responsible for ensuring the correct completion of the web-based questionnaires with the corresponding code. Participants who do not meet the inclusion criteria will have their questionnaires deleted, and the informed consent forms for nonparticipants will be discarded by the professionals. Participants who meet the inclusion criteria will be interviewed. Interviews will be audio recorded for analysis purposes and erased afterward. The informed consent forms will be securely handed over by the professionals to the principal investigator in a sealed envelope. The professionals will also schedule the interview date and communicate the participant’s code number to the research team, ensuring that the interview and questionnaire data match. The research team will not have access to any personal identifying information, such as names.

For the quantitative phase (phase 2), participants will fill in anonymous web-based questionnaires, as outlined in the informed consent form. For security reasons, participants must complete the questionnaire at the center they attend. Allowing them to complete it at home could put them at risk because their aggressors could see their responses. Participants will submit their informed consent to a designated professional at the relevant health center, unit, or association. This professional will have a list of codes. They will have to assign one to each participant (unknown to them) and will have to enter it so that each participant can start or pick up the questionnaire where they left off the last time. The professional will collect all informed consent forms and submit them to the principal investigator in a sealed envelope. Throughout the study, the research team will not have access to any personal identifying information.

In both studies, the web-based closed questionnaires will be designed using LimeSurvey, a private platform that meets security standards and data protection regulations. The responses will be stored in a database under the supervision of one of the collaborating universities. Before commencing the studies, the questionnaires will be piloted with a sample of 10 women to address any issues related to content, usability, or technical functionality of the web-based platform.

### Phase 1: Qualitative Study (General Aim 1, Specific Objectives 1 to 4)

#### Overview

We will use a qualitative approach with a descriptive and exploratory design, conducting individual semistructured interviews. Focus groups are not considered due to the necessity of maintaining the anonymity of those experiencing IPV against women. The results of this phase will allow us to incorporate any additional relevant factors or health outcomes into the study’s second phase.

#### Participants

The study will be conducted in the province of Alicante in Spain. To detect possible differences, interviews will be conducted with 2 groups: first, adult women with CP who are currently experiencing IPV (group 1) and, second, women with CP who are in a partner relationship and have never experienced IPV or any other form of violence, as defined earlier (group 2).

We will initially interview 10 women from each group, progressively increasing the number of interviews until theme saturation is reached [126]. Both groups will include women with varying sociodemographic characteristics, levels of disabling pain, and trauma symptoms. However, the diversity between the 2 groups will be balanced, ensuring that both groups include equal numbers of women with disabling pain and those without.

#### Procedure

First, we will reach out to the organizations through which we plan to access both groups and request their collaboration. To contact women who have experienced or are experiencing IPV and women with CP, we will consult associations and support centers for IPV against women, CP associations, CP units, and primary health care centers. These organizations will be asked to inform their patients about the project and encourage their participation.

Eligible candidates will be required to complete a series of questionnaires (refer to the Instruments subsection) to determine whether they meet the inclusion and exclusion criteria. The data from those who do not meet the criteria will be discarded. Those who qualify will proceed to complete additional questionnaires. The answers from these questionnaires will help us form the 2 groups while ensuring diversity based on age, racial background, and degree of disabling CP.

The inclusion criteria for both groups will be as follows: (1) women aged ≥18 years, (2) in a heterosexual intimate relationship for at least 1 year (as per Spanish law, IPV against women pertains to violence perpetrated by male intimate partners) [15], and (3) living with a CP condition highly prevalent in women and among those who have experienced IPV against women (eg, fibromyalgia, abdominal pain, genitourinary tract pain, pelvic and genital pain, headaches [including migraines], back and neck pain, and chronic fatigue syndrome) [19-22]. Women belonging to group 1 will, in addition, have to be currently experiencing IPV.

The exclusion criterion for group 2 will be having previously experienced IPV against women or any other form of violence because this may affect their current intimate relationships. The exclusion criterion for both groups will be experiencing oncological pain.

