Other studies have shown that those who have experienced IPV and are living with sickle cell disease are 5 times more likely to report CP than those who have never experienced IPV [24]. In addition, they are nearly twice as likely to develop fibromyalgia and chronic fatigue syndrome [25]. A recent systematic review and meta-analysis found strong and consistent associations between women who have experienced violence—whether by a partner or others—and CP conditions [26]. Furthermore, IPV against women is often linked to disabling pain [8,23,27]. Survivors with disabilities are more likely to report generalized CP than those with other disabling health conditions [28], and more than one-third continue to experience a high level of pain-related disability long after ending the abusive relationship [29].

Women who have experienced IPV also frequently use medication to alleviate pain [30]; for example, individuals with sickle cell disease who have experienced interpersonal violence are more than 6 times as likely to use opiate-based medications daily compared to those without a history of violence exposure [24].

Given the increased likelihood of those with exposure to IPV against women developing disabling CP and experiencing worse health outcomes [23,24,28,30]—even after leaving a violent relationship [29]—it is possible that experiencing (or having experienced) IPV against women influences the risk and protective factors involved in the development and maintenance of disabling CP differently. While previous studies have examined factors that predict or contribute to CP in those with exposure to violence [31,32], to our knowledge, no comparative studies have explored whether the underlying factors of CP differ based on a history of interpersonal violence.

Gathering this information is crucial for early detection and tailored treatment strategies for CP management in women who have experienced IPV as well as those who have not. Some researchers suggest that women with CP who are experiencing IPV may require more holistic care and support [26]. In addition, there is a need to better understand the daily experience of women living with CP while currently experiencing IPV compared to that of women who experience CP without a history of experiencing violence. However, no studies on this topic were found in the reviewed literature. In fact, the intersection of CP and IPV against women as interrelated phenomena has received little research attention [23].

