#### Sample Size Calculation

To calculate the sample size, the prevalence of the pain-avoidance activity pattern was used, which is typically present in cases of highly disabling CP [102]. Specifically, we considered several factors: first, the expected prevalence ratio assumed to be 2.0 between individuals with CP who are exposed to IPV against women and those who are not. Second, we estimated the prevalence of the pain-avoidance activity pattern within the study population, assuming it to be approximately 20%. While a previous study found that 40.4% of patients with fibromyalgia exhibited this pattern [133], we decided to use a more conservative estimate, given that the prevalence of this behavior is likely lower among the broader population of patients with CP. Finally, we accounted for the expected prevalence of IPV exposure among women with CP, estimated at 30% based on findings from earlier research [23].

We have defined the risk level α as 5% and the study power as 90%. The program used for size calculation was a macro, !NSize, for SPSS Statistics [134]. On the basis of these parameters, the required sample size consists of 359 women with CP: 193 (53.8%) with CP alone, 83 (23.1%) with CP and a current history of IPV, and 83 (23.1%) with CP and a past history of IPV.

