#### Procedure

We will access the sample through the same channels as in phase 1. First, we will explain the benefits of the project to the organizations and request their support in encouraging their patients to participate. The directors of these organizations will receive the link to the web-based questionnaire, which will then be distributed to patients who, for security reasons, can only complete the questionnaire at the respective facilities.

Participants willing to participate will have to complete a web-based questionnaire. The first page will outline the objectives of the study, and the second page will ask participants to confirm whether they meet the inclusion criteria, as described in the phase 1 Procedure subsection. Specifically, participants must be women aged ≥18 years and must have been living with one of the identified types of CP for at least 3 months.

Participants will have 1 month to complete the questionnaire. During this period, answers will be saved in the system to allow participants to complete the questionnaire on different occasions; however, as stated, the professionals at the centers will need to activate the survey links. Survey links are deactivated to prevent respondents from completing the questionnaires outside of the designated locations. The data will be automatically stored in a database, and the progress of sample collection will be monitored weekly to ensure that each group reaches the necessary sample size.

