#### Variables and Instruments

The variables and instruments that will be used, organized by purpose, are summarized in Table 2 and described in the subsections that follow. Some response scales will be alternated to identify biases in participants’ responses.

**Table 2 table2:** Variables and instruments used in study 2, organized by purpose.

Variable	Questionnaire	Control purposes^a^	Data analysis
Chronic pain	1 screening item	✓	
Sociodemographic characteristics	Ad hoc questionnaire	✓	✓
Access to the study	Ad hoc question	✓	
IPV^b^ against women	European Union Agency for Fundamental Rights study on violence against women survey inventory		✓
Possible traumatic events experienced	Adapted version of Life Events Checklist for DSM-5	✓	✓
Disabling chronic pain	GCPS-R^c^		✓
Severity of PTSD^d^ symptoms	EGS-R^e^		✓
Gender norms and gender identity	CFNI-45^f^		✓
Activity patterns	APS^g^		✓
Exercising	IPAQ^h^		✓
Pain worrying (pain catastrophizing)	PCS^i^		✓
Pain-related self-efficacy	CPSS^j^		✓
Informal social support	ISSADI-PAIN^k^		✓
Health related quality of life	MOS SF-12^l^		✓
Physical functioning	BPI- SF^m^		
Anxiety and depression	HADS^n^		✓
Suicide attempts and thoughts	Ad hoc questionnaire		✓
Medication use and illegal drug use	Ad hoc questionnaire		✓
Health service use	Ad hoc questionnaire		✓

^a^We include compliance with the inclusion and exclusion criteria.

^b^IPV: intimate partner violence.

^c^GCPS-R: Graded Chronic Pain Scale Revised.

^d^PTSD: posttraumatic stress disorder.

^e^EGS-R: Escala de Gravedad de Síntomas Revisada (Posttraumatic Stress Disorder Symptom Severity Scale-Revised)

^f^CFNI-45: Conformity to Feminine Norms Inventory-45.

^g^APS: Activity Patterns Scale.

^h^IPAQ: International Physical Activity Questionnaire.

^i^PCS: Pain Catastrophizing Scale.

^j^CPSS: Chronic Pain Self-Efficacy Scale.

^k^ISSADI-PAIN: Informal Social Support for Autonomy and Dependence in Pain Inventory.

^l^MOS SF-12: Medical Outcomes Study Short-Form Health Survey-12.

^m^BPI-SF: Brief Pain Inventory–Short Form.

^n^HADS: Hospital Anxiety and Depression Scale.

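### Phase 2 collects pain type but does not mark it for analysis, so a different mix of pain conditions between groups may be read as an IPV profile, or may hide one

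*Protocol article*

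**What the plan says.** **Who is eligible.** The third inclusion criterion in the phase 1 Procedure is "living with a CP condition highly prevalent in women and among those who have experienced IPV against women", with examples from fibromyalgia and headache to pelvic, back and neck pain and chronic fatigue syndrome. The phase 2 Procedure refers back to these criteria: women "must have been living with one of the identified types of CP for at least 3 months". No balancing of conditions across the three groups is described.

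**Condition and IPV.** The Background says that women exposed to IPV report more fibromyalgia, along with several other pain conditions. It adds that "they are nearly twice as likely to develop fibromyalgia and chronic fatigue syndrome".

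**Condition and outcome.** The Sample Size Calculation notes that "a previous study found that 40.4% of patients with fibromyalgia exhibited this pattern". It sets the planning value by "assuming it to be approximately 20" percent, on the ground that "the prevalence of this behavior is likely lower among the broader population of patients with CP".

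**What is done with pain type.** Phase 1 (CP and Type) has each woman choose her type from a list, and phase 2 adopts that item among its control variables. In Table 2 chronic pain is "1 screening item", ticked for control purposes and not for data analysis. The phase 2 list of sociodemographic risk and protective factors keeps only whether there is a diagnosis and the years since it. The phase 2 Data Analysis section describes t tests, ANOVA, feature ranking and classifiers, and none of them names pain type.

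**The concern.** Phase 2 asks whether women with chronic pain alone, with current IPV and with past IPV have distinct profiles, and which factors best explain them. Suppose the groups differ in their share of fibromyalgia, and fibromyalgia goes with more avoidance whatever the IPV history. A comparison that ignores pain type then mixes two things: differences between women with the same condition, and differences in which conditions they have. A classifier that is not offered pain type cannot show which of the two it has found.

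This bears on interpretation. The Limitations section foresees attributing replicated profiles largely to IPV, and the findings are to feed assessment and intervention guidelines. The opposite error is also possible: if the group with pain alone holds more fibromyalgia, a real difference could be masked.

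**Working it through.** **1. The plan's own figure.** Inputs from the Sample Size Calculation: p0 = 0.20, prevalence ratio 2.0 so p1 = 0.40, 30% exposed so k = 3/7, alpha 5% (taken as two-sided), power 90%.

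- Pooled p = (0.20 + 0.40 × 3/7)/(1 + 3/7) = 0.26.
- n0 = [1.960 × √(3.333 × 0.26 × 0.74) + 1.282 × √(0.16 + 0.24 × 7/3)]² / 0.20² = 176.5.
- With the continuity correction, n0 = (176.5/4) × [1 + √(1 + 2 × 3.333/(176.5 × 0.20))]² = 192.8, so 193. n1 = 192.8 × 3/7 = 82.6, so 83.
- 193 + 83 + 83 = 359, as stated.

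The planned contrast is therefore 20% against 40%, with 193 against 83 women.

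**2. Avoidance from condition mix alone.** Take 40.4% in fibromyalgia and 20% overall in women with pain alone. *Assumptions, because the protocol gives no shares:* the fibromyalgia share f in women with pain alone is 10%, 20% or 30%; the odds of fibromyalgia are doubled in IPV women; IPV has no effect within condition.

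- Avoidance in other conditions: q = (0.20 − 0.404f)/(1 − f)
- Fibromyalgia share in IPV women: f1 = 2f/(1 + f)
- Avoidance in IPV women: p = 0.404 × f1 + q × (1 − f1)

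| f | q | f1 | p | p/0.20 |
|---|---|---|---|---|
| 0.10 | 0.177 | 0.182 | 0.219 | 1.09 |
| 0.20 | 0.149 | 0.333 | 0.234 | 1.17 |
| 0.30 | 0.113 | 0.462 | 0.247 | 1.24 |

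As an illustration, a two-sided 5% two-proportion test of 193 against 83 would show a significant excess in 5.6%, 9.8% or 14.6% of studies, against a nominal 2.5% in that tail. The protocol plans comparisons of means, so these rates indicate scale only.

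**3. Read the other way.** Under the same assumptions, an observed 20% against 40% would correspond to a condition-standardised ratio of 0.40/p = 1.83, 1.71 or 1.62.

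**4. Sensitivity.**

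- If the other conditions also rise 1.5-fold with IPV (assumption), the relative odds of fibromyalgia are 2/1.5 = 1.33 and the ratios are 1.03, 1.06 and 1.09. If they double too, the ratio is 1.00.
- If recruitment puts more fibromyalgia in the group with pain alone, say 30% against 15% or 40% against 20% (assumption), the ratio is 0.78 or 0.66.

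**5. Cost of adjustment.** The variance inflation from adding fibromyalgia (yes/no) is 1/(1 − φ²), where φ is the correlation between fibromyalgia and group. For the three rows above it is 1.013, 1.021 and 1.025. Keeping the planned precision would take about 366, 368 or 370 women in place of 359.

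**The case against.** The other side has good points, and several of them stand.

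- **Pain type is used only for screening.** A reader might infer this from Table 2, but the document does not support it. The column is headed control purposes, and its footnote says that eligibility checks are included, not that they are all. How the woman reached the study is ticked there too and is not an eligibility item. What stands is narrower: pain type is not marked for analysis, and no analytic use is described.
- **A missing tick is weak evidence.** The Brief Pain Inventory has no tick in either column, yet other sections make it an outcome. Adjustment sets are often left to an analysis plan. But for pain type no other phase 2 section supplies a use, and the factor list covers diagnosis without type.
- **The figures cover one condition and one pattern.** Only fibromyalgia has an avoidance figure, and the 20% is a planning assumption. Nothing ties fibromyalgia to more pain worrying, disability or drug use than the other eligible conditions. Avoidance served for sample size and is not declared the key outcome. The sentence on doubled likelihood follows one about sickle cell disease, so its subject is ambiguous, although the preceding Background text supports the direction.
- **The fibromyalgia share doubles.** A reader might take this from the Background and reach ratios of 1.11 to 1.44. But that statement concerns developing the condition; among women who all have chronic pain it does not double the share. The odds reading is closer, and even that ignores the other conditions reported more often after IPV.
- **A condition mix is itself a profile.** The study is descriptive and calls itself preliminary, and pain type may be partly a consequence of IPV. This stands. It rules out treating the adjusted result as the only valid one.

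**Conclusion.** The point holds for phase 2 in a limited form. The protocol admits mixed conditions, links fibromyalgia to both IPV and avoidance, collects pain type, and then describes an analysis that does not use it. A difference in condition mix may therefore be read as an IPV profile, or may conceal one.

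It is not established that this will happen, or in which direction. Group shares are unknown, and the recruitment channels differ: IPV support centres, pain associations, pain units and primary care. With 10% to 30% fibromyalgia in women with pain alone, doubled odds in IPV women and no effect within condition, mix alone gives a ratio of about 1.09 to 1.24. It is less if other conditions also rise with IPV, and below 1 if fibromyalgia is concentrated in the group with pain alone. In none of these cases does it reach the planned 2.0, so a reader should not infer that condition mix could account for the whole planned effect.

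**What to change.** - In Table 2, mark pain type for data analysis, and add it to the phase 2 list of risk and protective factors.
- Report the mix of conditions by group and by recruitment channel; both items are already collected.
- Present the group comparisons overall and again adjusted for, or stratified by, pain type (at least fibromyalgia against other).
- Run the feature ranking and classifiers with and without pain type.
- Interpret the two sets side by side. Because pain type may lie on the path from IPV to outcome, do not require a difference to persist within condition before describing a group profile.

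The cost is a table tick, one added factor and a second set of estimates. No new item is needed. The loss of precision is small (variance inflation about 1.01 to 1.03 under the assumptions above), though sparse conditions will need to be grouped.
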